#### Aim 3: To evaluate the effect of CAP on changes in Life Simple-7 (LS7) scores.

We hypothesize that participants in the CAP arm will have improvement in LS7 scores compared to RAU at 6-months and 1 year.

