The power analysis equation for 2 follow ups examined in aim 3 is: $m=2g{\left(z_{\alpha }+z_{\beta }\right)}^{2}\sigma (1-\left.r_{c}^{2}\right)\sum \sum r_{ij}/{\left(R_{el}\sum d_{i}\right)}^{2}$, and $r_{c}=\sum r_{i1}/\sqrt{\sum \sum r_{ij}}$, where g is the clustering adjustment for church, *r*_*ij*_ is the correlation matrix for 2 follow-ups, *r*_*i*1_ is the correlation between baseline and 2 follow-ups and di is the follow-up difference between 2 groups for two follow-ups, with i=1,2 and j=1,2. The correlation between the baseline and 2 follow ups (half year, 1 year) will be modeled as CS (compound symmetry (constant: *r*_*i*1_ = *ρ*, *ρ*)) and AR_1_ (Autoregressive (Exponential decay, $r_{i1}=\sqrt{\rho },\rho$)). The difference between the 2 follow-ups will be modeled as unequal: *d*_*i*_=(¾d, d) -- the half year follow-up difference between 2 groups is ¾ of the 1 year study-end difference; and equal: *d*_*i*_=(d, d) -- the two follow up group differences are the same. The minimal detectible effect size (expressed as Cohen’s d) with m subjects per group was calculated assuming: α=0.05 (two-tailed), *R*_*e*_(reliability), g=1.57 (clustering adjustment for church as descripted above), m=198 per group at 6 month follow up assuming at least 2 waves of data and an intent-to-treat (ITT) model for the third wave (220 subjects at baseline, 10% attrition at 6-month follow-up). The correlation between baseline and 1 year follow up is assumed to be 0.5, 0.6 and power=80%. Two scenarios regarding the covariance structure and the difference between groups were also examined.

Dietary inflammation score (DIS): For the DIS outcome, with baseline and one follow up, it is assumed that σ=1 for the standardized score. Assuming α = 0.05 for a two-tailed test, 10% attrition, with m= 198 per group at 6 months (220 at baseline, 11 churches per group), adjusting for reliability=0.8 and the clustering effect of church, it will be possible to detect a small effect size of δ=0.303 (Cohen’s d=0.303), with power of 0.80. With the correlation between baseline and follow up equal to 0.6, the Cohen’s d=0.280 (an effect size of δ=0.280).

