For the LS7 outcome, with baseline and two follow ups, it is assumed that σ=2.7 (standard deviation). Assuming the difference between the 2 groups is unequal will result in lower power than if equal. A correlation structure of compound symmetry will result in lower power than autoregressive (AR). The primary analyses assume ITT for the 3rd wave, α = 0.05 for a two-tailed test. However, effects assuming 20% attrition, with m = 176 per group at 1 year study-end were also calculated (baseline m=220, 6-month m=198 and 1 year m=176). With an m = 198 per group at 6-months (ITT model for 3rd wave), it will be possible to detect an effect size of δ=0.764 (Cohen’s d=0.283), with power of 0.80. With the correlation between baseline and follow up equal to 0.6, the Cohen’s d=0.265 (which translates to an effect size of δ=0.716). Examining different scenarios regarding the difference between the groups and the correlation structure of compound symmetry, or AR, the detectable effect sizes range from δ=0.645 (Cohen’s d=0.239) to δ=0.810 (Cohen’s d=0.300) with power of 0.80.

#### Analysis for Aim 1

Logistic-type regression analyses will be used to test the hypothesis that those assigned to SBIRT will have significantly higher CRC screening rates compared to those randomized to RAU at 6 months. Clustered sampling effects due to churches will be incorporated using a multilevel modeling approach. Ideally, the randomization of participants to treatment arm and the absence of significant selection and/or attrition biases will obviate the need for inclusion of covariates. In the event that the logit analyses indicate one or more sources of potential bias, the predicted values of those analyses will be included as covariates in a multilevel logistic regression model (SAS, PROC GLIMMIX).

#### Analysis for Aims 2 and 3

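### The detectable LS7 difference of 0.764 matches a one-sided quantile with 198 per arm at both visits; at the stated two-tailed 0.05 it is about 0.86 to 0.91, and the range beside it belongs to 176 per arm

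*Protocol article*

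**What the plan says.** Aim 3 (Objectives {7}) states: "We hypothesize that participants in the CAP arm will have improvement in LS7 scores compared to RAU at 6-months and 1 year".

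The rest is in Statistical methods {20a}, under the power analysis for Aims 2 and 3:

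- The formula for two follow-ups has the squared sum of the two group differences in its denominator. In the unequal scenario "the half year follow-up difference between 2 groups is ¾ of the 1 year study-end difference"; in the other scenario the two differences are equal.
- "The correlation between baseline and 1 year follow up is assumed to be 0.5, 0.6 and power=80"%. The clustering factor g is 1.57.
- For LS7, "it is assumed that σ=2.7 (standard deviation"), and "The primary analyses assume ITT for the 3rd wave, α = 0.05 for a two-tailed test".
- With m = 198, "it will be possible to detect an effect size of δ=0.764" (Cohen's d 0.283), or 0.716 (d 0.265) when the correlation is 0.6.
- Across scenarios, the detectable differences run from 0.645 (d 0.239) to 0.810 (d 0.300).
- On attrition: "However, effects assuming 20% attrition, with m = 176 per group at 1 year study-end were also calculated", with 220 at baseline and 198 at 6 months.

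A reliability of 0.8 is stated for the dietary inflammation score (DIS). None is stated for LS7.

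**The concern.** Three things do not fit together.

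1. The protocol says that unequal differences and compound symmetry each lower power. The headline already combines both at the lower correlation, so no listed scenario with m = 198 can need a larger difference than 0.764. Yet the range reaches 0.810.
2. The Aim 1 formula is written with the 1−α/2 quantile. The formulas for Aims 2 and 3 are written with z at α, although the text says two-tailed.
3. The hypothesis names two visits, but the calculation sizes one contrast that combines them.

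At stake is how an LS7 result is read. Someone who takes 0.764 as detectable with 80% power, and then sees a non-significant result at one visit, would give that result more weight than the design supports.

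**Working it through.** **Inputs.** From the protocol: g = 1.57; SD 2.7; ρ = 0.5 or 0.6; 198 per arm at 6 months and 176 at 1 year; power 80% (z = 0.842). Assumed: LS7 reliability R = 0.8, applied once. The printed formula has σ unsquared and R inside the squared term; I use the standardised form, which matches the figures.

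**Quantile, checked on DIS, where R = 0.8 is stated.** d = √[2g(zα+zβ)²(1−ρ²)/(mR)] with m = 198:

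| | ρ = 0.5 | ρ = 0.6 |
|---|---|---|
| Stated | 0.303 | 0.280 |
| z = 1.645 | 0.3032 | 0.2801 |
| z = 1.96 | 0.3416 | 0.3156 |

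**LS7 headline.** d = √[2g(zα+zβ)² × V/(mR)] / w. Here V is the sum of the follow-up correlation matrix minus the squared sum of the baseline correlations. The divisor w is 1.75 for (¾d, d) and 2 for (d, d).

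- Compound symmetry, ρ = 0.5: V = 3 − 1 = 2. With z = 1.645, (1.645+0.842)² = 6.183, so d = √[3.14 × 6.183 × 2/158.4]/1.75 = 0.283. Times 2.7 this is 0.764, as stated.
- ρ = 0.6: V = 3.2 − 1.44 = 1.76, d = 0.2654 (stated 0.265).

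So 0.764 is the 1-year difference. The implied 6-month difference is 0.75 × 0.764 = 0.573, and the average is 0.669.

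**Range, z = 1.645.** The lower end is AR, ρ = 0.6, equal differences. The upper end is compound symmetry, ρ = 0.5, unequal.

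| m | Lower d (points) | Upper d (points) |
|---|---|---|
| 198 | 0.2255 (0.609) | 0.2829 (0.764) |
| 176 | 0.2392 (0.646) | 0.3001 (0.810) |
| Stated | 0.239 (0.645) | 0.300 (0.810) |

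I varied the reliability from 0.6 to 1.0 (once or squared), m over 176, 187, 198 and 220, and both quantiles. The two headline values and both ends of the range match together only with z = 1.645, an effective reliability factor of about 0.8, m = 198 for the headline and m = 176 for the range.

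**Pooled test at the stated two-tailed 0.05.** (1.96+0.842)² = 7.849.

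- 198 at both visits: d = √[3.14 × 7.849 × 2/158.4]/1.75 = 0.3188, or 0.861 points. Power at d = 0.283 is Φ(2.802 × 0.283/0.3188 − 1.96) = 70%. Keeping 80% at that effect would need about 198 × (0.3188/0.283)² = 251 per arm.
- 176 at both visits: 0.861 × √(198/176) = 0.913.
- 198 at 6 months, 176 of them at 1 year, likelihood-based. Given baseline, each visit has variance 0.75 and the covariance is 0.25, so the regression slope is 1/3. The summed contrast has variance (4/3)² × 0.75/198 + (0.75 − 0.25²/0.75)/176 = 0.010522, against 2/198 = 0.010101. The detectable difference is 0.861 × √1.0417 = 0.88.

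**Single visits in the headline scenario.** SE = √[2g(1−ρ²)/(mR)], which is 0.1219 for m = 198 and 0.1293 for m = 176.

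| Visit | d | Power, z = 1.96 | Power, z = 1.645 | Two-tailed detectable points |
|---|---|---|---|---|
| 6 months, m = 198 | 0.212 | 41% | 54% | 0.92 |
| 1 year, m = 176 | 0.283 | 59% | 71% | 0.98 |

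Under AR with equal differences, the 6-month correlation with baseline is √0.5 and SE = 0.0996. Two-tailed 6-month power at d = 0.283 is then 81%.

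**The case against.** The protocol is open about pooling: it introduces a formula for two follow-ups and describes LS7 as having a baseline and two follow-ups. Its basic analysis model for Aims 2 and 3 has a single group coefficient, which fits a pooled effect. How the visits are tested may be set out in an analysis plan that is not shown. The 1-year attrition is disclosed, and LS7 is a secondary outcome that does not drive the sample size. All of this stands.

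It rules out several stronger readings that a reader might infer:

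- *The protocol claims 80% power at each visit.* It states no per-visit LS7 power. The gap is that Aim 3 names two visits and the published figure describes neither alone.
- *0.764 is the average difference.* It is the 1-year difference; the average is 0.669.
- *No single visit can reach 80%.* That holds in the headline scenario, but 6-month power is about 81% under AR with equal differences at the same d.
- *The loss at 1 year is concealed.* The figure of 176 is printed; only the label on the range is missing.
- *0.810 is the correct headline.* It takes 176 at both visits and keeps the one-sided quantile. The mixed model keeps people seen only at 6 months, so the planned attrition alone raises 0.764 only to about 0.78.

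None of this explains why figures described as two-tailed match 1.645, or why the range follows the m = 198 headline without its own m.

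**Conclusion.** The point holds for the stated figure. The LS7 difference detectable with 80% power at two-tailed 0.05 is not 0.764. In the headline scenario it is 0.861 with 198 per arm at both visits, about 0.88 under the planned attrition and 0.913 with 176 at both. The quantile accounts for most of the gap and attrition for little. The printed range is an m = 176 range; on the same quantile, the m = 198 range is 0.609 to 0.764.

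The single-visit figures show what the pooled calculation does not cover; they do not contradict a claim in the protocol.

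The main assumption is the LS7 reliability of 0.8, inferred because it reproduces all the LS7 figures. The DIS figures, for which 0.8 is stated, point to the same one-sided quantile. The per-visit powers also depend on the correlation structure and the pattern of differences.

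**What to change.** In the power analysis for Aims 2 and 3:

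- Recompute the LS7 detectable differences with the two-tailed quantile and with 198 at 6 months and 176 at 1 year, and state the LS7 reliability used.
- Give the scenario range with its m.
- Say that the headline value is the 1-year difference under the (¾d, d) pattern.
- Name the pooled 6- and 12-month contrast, which is what was sized, as the Aim 3 test, with each visit as a secondary estimate.
- State the single-visit detectable differences, about 0.92 at 6 months and 0.98 at 1 year in the headline scenario.

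The cost is a recalculation, some wording and less favourable published figures for a secondary outcome. Recruitment does not change.

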$\text{logit}(p)=\text{log}\left(\frac{p}{1-p}\right)=\beta_{0}+\beta_{1}X+\tau_{c}$ where X is a binary variable (0 for usual care and 1 for SBIRT intervention), *τ*_*c*_ is a random effect for clustering within churches, and p = prob(Y=1, CRC screening rate). The hypothesis H_0_: *β*_1_ = 0 vs H_1_: *β*_1_ = *β** will be tested with the formula for determining the total sample size.^58–61^: $n^{*}=\frac{{\left(V{\left(0\right)}^{1/2}Z_{1-\alpha /2}+V{\left(\beta^{*}\right)}^{1/2}Z_{1-\beta }\right)}^{2}}{P_{1}\beta^{*2}}\left(1+2P_{1}\delta \right)$ with $\beta^{*}=\text{log}\frac{P_{2}\left(1-P_{1}\right)}{P_{1}\left(1-P_{2}\right)}$, with $V(0)=\frac{1}{1-B}+\frac{1}{B}$, $V\left(\beta^{*}\right)=\frac{1}{1+B}+\frac{1}{\text{Bexp}\left(B^{*}\right)}$, *δ* = (*V*(0)^1/2^ + *V*(*β**)^1/2^*R*)/(*V*(0)^1/2^ + *V*(*β**)^1/2^), *R* = *v*(*β**)*B*(1 − *B*) exp(2*β**)/(*Bexp*(*β**) + (1 − *B*))^2^, where *P*_1_, *P*_2_ are the CRC screening rates of usual care and SBIRT (intervention), respectively, and B is the proportion of the sample assigned to each of two arms (B=0.5), *δ* is a small rate adjustment, when *P*_1_ < 0.2 (*δ* = 0 when *P*_1_ ≥ 0.20), adjusting for unreliability and clustering (g=1+(s-1)*icc):*n* = *n***g*/*R*_*el*_. The assumptions are: for α=0.05 (2 tailed test), 1-β=0.80 (power), *R*_*el*_ = 0.95 (adjusted for unreliability), g=1.57 (variance inflation factor adjusting for clustering), with cluster size s=20 and icc (intracluster correlation coefficient=0.03). *P*_1_ (X=0, usual care group), *P*_2_ (X=1, intervention group), B=0.5, n=total sample size, and power for n=396 (m=198 per group, about 11 churches per group with attrition rate=10% at 6 months with an average of 20 participants per church)/

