Regarding the CRC screening rate, a sample size of 198 subjects per group (10 to 12 churches per group, average of 20 subjects per church, attrition rate of 10% at 6 months) is required to provide 80% or greater power to detect a group difference of 15% (a clinically meaningful increase) in the rates of completed colorectal cancer screening at 6 months. Thus, power will be sufficient to detect the hypothesized difference from baseline in both arms. As shown above, these calculations assume a baseline rate of 0 and scenarios with increase in screening rates in the usual care group from 0.20 to 0.50. Thus, with an overall sample size of 440 subjects or 220 per arm (11 churches per arm with 20 subjects in each church), the study is powered adequately, even with attrition. Based on our prior study in which approximately 50% of AAs above age 50 years were not up to date with screening,^48^ we will screen at least 40 adult churchgoers aged 45 years and older per church for study eligibility (total screening = 880 subjects).

#### Power analysis for Aims 2 and 3

Aim 2 is to evaluate the effect of a CAP incorporated into the intervention arm on DIS at baseline and 6-month follow up; and Aim 3 is to evaluate the effect of CAP on changes in LS7 at baseline, 6-months and 12 months. Sensitivity analyses will be performed including data from the 3-month wave. Power calculations were performed for an analysis of covariance (ANCOVA)-type model: *y*_*ijk*_ = *μ*_*jk*_ + *y*_*i*0_ + *τ*_*c*_ + *e*_*ijk*_, where *μ*_*jk*_ is the group mean for follow up DIS and LS7, *y*_*i*0_ is the baseline measure, j=1,2 follow-ups and k=0, 1 for group, *τ*_*c*_ is a random effect for clustering within church. The power analysis equation for one follow-up is: $n=\frac{2{\left(z_{\alpha }+z_{\beta }\right)}^{2}\sigma^{2}\left(1-\rho^{2}\right)g}{d^{2}R_{el}}$: where *ρ* is the correlation between the outcome and baseline values, *σ* is the standard deviation, *d*_*I*_ is the follow-up difference between 2 groups, *R*_*el*_ is the reliability of the outcome, adjusting for clustering within churches, g=1+(s-1)*icc, and n is number of subjects per group.

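### Aim 1 is sized with normal quantiles although the arm effect rests on 22 churches, so a nominal 80% power is about 76% once the 5% level is held

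*Protocol article*

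**What the plan says.** All references are to the Protocol article.

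- **Design.** Trial Design {8} gives 11 churches per arm. Sequence Generation {16a} matches churches on membership size and randomises them 1:1.
- **Sizing, Power analysis for Aim 1.** The logistic formula uses standard normal quantiles for both error and power: "The assumptions are: for α=0.05 (2 tailed test), 1-β=0.80 (power"). Clustering enters through a design effect, "g=1.57 (variance inflation factor adjusting for clustering"), "with cluster size s=20 and icc (intracluster correlation coefficient=0.03"). The result is given as "power for n=396 (m=198 per group, about 11 churches per group with attrition rate=10% at 6 months".
- **Conclusion drawn.** The sample of 198 per group "is required to provide 80% or greater power to detect a group difference of 15" per cent, for usual-care rates from 0.20 to 0.50, and the section ends by calling power adequate after attrition.
- **Test, Analysis for Aim 1.** The church effect is handled as follows: "Clustered sampling effects due to churches will be incorporated using a multilevel modeling approach". SAS is named for the version with bias-correcting covariates, a "multilevel logistic regression model (SAS, PROC GLIMMIX"). No reference distribution or degrees-of-freedom method is given for the arm effect.
- **Aims 2 and 3.** The sizing formulas also use z quantiles. The power model contains a church random effect; the basic analysis model printed under Analysis for Aims 2 and 3 does not.

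**The concern.** The design effect and the choice of quantile do different jobs. The factor 1.57 makes the variance of the arm effect larger because participants share a church. It does not allow for the between-church variation being estimated from only 22 churches. That second uncertainty belongs in the reference distribution: t with 22 − 2 = 20 df, or 11 − 1 = 10 df if the matching is analysed as 11 pairs.

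The sizing gives 80% power only if the final test also uses the normal critical value of 1.96, and with 22 churches such a test exceeds 5%. If the test is calibrated to the number of churches, the 5% level is held and the stated power is too high. Either way, one of the two stated properties of the primary analysis is not delivered where the sizing has no slack.

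**Working it through.** **Inputs (Power analysis for Aim 1):** two-sided α = 0.05, power 0.80, B = 0.5, δ = 0 for P1 ≥ 0.20, s = 20, ICC = 0.03, reliability 0.95, analysed n = 396, difference 0.15, P1 from 0.20 to 0.50. **Assumption:** the printed first term of V(β*), 1/(1+B), is read as 1/(1−B), as in V(0). The printed form gives n = 349 at P1 = 0.20, which does not match the plan's figure.

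**Step 1, design effect.** g = 1 + 19 × 0.03 = 1.57, as stated.

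**Step 2, reproduce the plan's figure.** n = [√V(0)·1.960 + √V(β*)·0.842]² / (P1·β*²) × g/0.95, with V(0) = 4 and V(β*) = 2 + 2/exp(β*). At P1 = 0.20 and P2 = 0.35, β* = log(0.35 × 0.80 / (0.20 × 0.65)) = 0.767 and V(β*) = 2.929. This gives n* = 244.0 and n = 244.0 × 1.57/0.95 = 403. At P1 = 0.25 the result is 398. Both are close to 396, so the plan's figure is reproduced at about 80% power with normal quantiles.

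**Step 3, the df penalty alone.** An 80% design under normal quantiles has noncentrality 1.960 + 0.842 = 2.802.

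- 20 df: critical value 2.086, power 76.0%.
- 10 df: critical value 2.228, power 71.4%.
- Restoring 80% on 20 df would take about 10.5% more information (396 × 1.105 ≈ 438 analysed).

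**Step 4, the plan's formula at n = 396 with t on 20 df.** Normal-quantile power is Φ{[√(396 × 0.95/1.57 × P1)·β* − 2 × 1.960]/√V(β*)}. The noncentrality is 1.960 plus the normal quantile of that power, and it is then referred to noncentral t with 20 df.

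| P1 | n from plan's formula | power, z | power, t on 20 df |
|---|---|---|---|
| 0.20 | 403 | 79.2% | 75.1% |
| 0.25 | 398 | 79.8% | 75.7% |
| 0.30 | 383 | 81.5% | 77.5% |
| 0.35 | 359 | 84.1% | 80.3% |
| 0.40 | 328 | 87.4% | 84.0% |
| 0.50 | 251 | 94.8% | 92.7% |

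The z powers just under 80% in the first two rows are rounding. On 20 df, power is below 80% up to about P1 = 0.30 and reaches it from about 0.35.

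**Step 5, size if a normal reference were used.** P(|t| > 1.96) is 6.4% on 20 df and 7.8% on 10 df. Trials of 22 churches × 18 participants were simulated with ICC 0.03 and no effect, and analysed with a random-intercept logistic model (3,000 per scenario, Monte Carlo standard error about 0.4 points). At rates 0.20, 0.35 and 0.50 they rejected 5.9%, 7.0% and 6.5% of the time with z, and 4.6%, 5.7% and 5.2% with t on 20 df.

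**The case against.** **The df method belongs in the SAP.** This stands for the analysis text. A multilevel model with a church effect is correct as far as it goes, and silence on a df option in an article is no defect. It does not rescue the sizing, which is stated here together with its conclusion. No later choice of df method makes both 5% and 80% true at the lower usual-care rates.

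**A reader might infer that both properties fail.** They do not fail together. With z, the size is inflated and power is as computed. With t on 20 df, the size is held and power falls by about 4 points.

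**A reader might infer that the primary test is a z test because PROC GLIMMIX is named.** The protocol states no reference distribution and gives no code, and it names the procedure only for the covariate-adjusted version. The 6.4% is therefore conditional.

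**A reader might attribute a much larger power loss to this point.** A standard two-proportion variance with 198 per arm, g = 1.57 and reliability 0.95 gives 75.1% (z) and 70.9% (t on 20 df) at P1 = 0.20, and 66.1% and 61.8% at 0.35. Those figures start low because the variance formula differs. Only the step of about 4 points belongs here.

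**The sizing carries margins.** With 18 analysed per church, g would be 1 + 17 × 0.03 = 1.51, and the reliability factor adds more: 1.57/1.51/0.95 = 1.094, against a penalty of 1.105. A nominal 80% design with both margins has 79.6% on 20 df. This stands only if the reliability inflation is spare. If 0.95 reflects real outcome error, as the plan assumes, the remaining margin is 1.57/1.51 = 1.040 and power is about 77.6%.

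**Normal quantiles with a design effect are a common approximation.** True, and clustering was not ignored. But at the low end of the stated range the calculation has no slack to absorb the approximation.

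**Conclusion.** The point holds as a modest, definite overstatement of Aim 1 power. With the 5% level protected on 20 df, a nominal 80% is about 76%. In the plan's own formula at 396 analysed, power falls short of 80% for usual-care rates up to about 0.30 and meets it from about 0.35. If the size-matched pairs are analysed as pairs, the nominal 80% becomes about 71%; the protocol does not say whether they will be.

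The result rests on the plan's ICC, design effect, reliability and attrition, on the reading of the misprinted variance term, and on t as the reference for a church-level contrast. Inflated type I error is a possibility left open by the text, not something the protocol commits to.

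**What to change.** 1. For the arm effect in the Aim 1 multilevel logistic model, name a small-sample df method based on churches, between-within or Kenward-Roger. State whether the size matching enters the model, so that the df agree with it.
2. Restate Aim 1 power across usual-care rates 0.20 to 0.50 with t quantiles for the existing 22 churches, and correct the printed variance term in the same edit.
3. For Aims 2 and 3, use the same kind of reference distribution and carry the church random effect from the power model into the printed analysis model. A df option alone would repair nothing there, because that model has no church term.

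The cost is one model option, one added term in the Aims 2 and 3 model, and a power figure about 4 points less favourable. No churches or participants need to be added. Trial Status expects recruitment to finish in 2027, so the change can be made before analysis.

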## Assignment of Interventions: Allocation

### Sequence Generation {16a}

In this study, randomization will occur on the church level to reduce chances of contamination through interactions between congregants in the same church. Four churches will be randomized in Years 1; six churches in Years 2; six churches in year 3; and six churches in year 4 to reach our target sample size of 22 churches. Churches will be matched based on size (number of members) and randomized in a 1:1 ratio to either SBIRT and ALIVE! or RAU. A randomization sequence will be generated by the study statistician according to CONSORT guidelines. Randomization will occur on the church level prior to the start of screening events to allow for assignment to specific booster trainings with the CHWs. At the end of data collection, churches assigned to the RAU arm will be offered SBIRT.

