An ANCOVA-type model, using SAS Proc Mixed will be used to allow for flexible modeling of assumptions, treatment of missing data and inclusion of all subjects with at least one wave of data. The basic model is: *Y*_*i*_ = *β*_0_ + *β*_1_*Y*_0*i*_ + *βX*_*i*_ + *e*_*i*_. Based on prior analytic experience with the outcome variables, it is not expected that transformations will be necessary; however, distributions will be examined for confirmation. The continuous longitudinal outcomes will be modeled as functions of baseline values, randomization groups, covariates and interactions as necessary. Prior to analyses, baseline values of all variables will be examined. Variables differing between the groups will be examined in secondary analyses.

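### The analysis model written for DIS and LS7 (Aims 2 and 3) omits the church random effect that the power model for the same outcomes includes

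*Protocol article*

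**What the plan says.** Under Sequence Generation {16a}, the Protocol article states that "randomization will occur on the church level to reduce chances of contamination through interactions between congregants in the same church". There are 22 churches, 11 per arm, with 20 participants planned in each.

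For the secondary outcomes, DIS at 6 months and LS7 at 6 and 12 months, the statistical methods section {20a} gives two models:

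- **Power analysis for Aims 2 and 3.** An ANCOVA-type model indexed by follow-up and group, with a term τ_c that "is a random effect for clustering within church". The detectable effects are then computed with "g=1.57 (clustering adjustment for church as descripted above), m=198 per group at 6 month follow up". For LS7, the correlation across waves is set out as compound symmetry or first-order autoregressive.
- **Analysis for Aims 2 and 3.** "An ANCOVA-type model, using SAS Proc Mixed will be used to allow for flexible modeling of assumptions". The equation that follows is: "The basic model is: *Y*_*i*_ = *β*_0_ + *β*_1_*Y*_0*i*_ + *βX*_*i*_ + *e*_*i". The accompanying text lists baseline values, randomisation groups, covariates and interactions as predictors. Church is not among them.

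The section Analysis for Aim 1, by contrast, is explicit: "Clustered sampling effects due to churches will be incorporated using a multilevel modeling approach". That sentence concerns screening rates and is not repeated for Aims 2 and 3.

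**The concern.** In a cluster-randomised trial the arm effect has to be judged against variation between churches. A model with only an independent participant-level error judges it against variation between individuals. Standard errors are then too small, intervals too narrow, and the test rejects too often under the null. Naming Proc Mixed does not repair this, because without a statement for church it fits an ordinary ANCOVA.

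The protocol's own power calculation inflates the sample size by 1.57 for church clustering, so the analysis equation is also inconsistent with the calculation that justifies these aims. Both quantitative secondary effectiveness claims, on diet and on cardiovascular risk, depend on which of the two models is used.

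**Working it through.** **Inputs from the protocol.** Cluster size and ICC: "with cluster size s=20 and icc (intracluster correlation coefficient=0.03". Alpha is 0.05 two-tailed. There are 11 churches per arm, with 220 participants per arm at baseline and 198 at 6 months after 10% attrition, so 198/11 = 18 per church at follow-up. Reliability for DIS is 0.8 and the baseline correlation ρ is 0.5.

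**Step 1: the protocol's design effect.** g = 1 + (s − 1) × ICC.

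- s = 20: 1 + 19 × 0.03 = 1.57, as stated.
- s = 18: 1 + 17 × 0.03 = 1.51.

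**Step 2: the church adjustment really is in the stated detectable effects.** The protocol's formula for one follow-up, solved for d, is d = √[2(z_α + z_β)²(1 − ρ²)g / (m × R_el)].

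- With g = 1.57: √[2 × (1.645 + 0.842)² × 0.75 × 1.57 / (198 × 0.8)] = 0.303, the stated value.
- Without g: 0.242.

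So the published DIS figure assumes a church effect. The match needs the one-sided quantile 1.645; the stated two-tailed alpha gives 0.342. That is a separate matter and does not affect this point.

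**Step 3: type I error if the analysis equation is fitted literally.** Ignoring clustering understates the standard error by a factor √g, so the true two-sided error is 2 × [1 − Φ(1.96/√g)].

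| ICC | 18 per church | 20 per church |
|---|---|---|
| 0.01 (assumed) | 7.0% | 7.2% |
| 0.02 (assumed) | 9.0% | 9.5% |
| 0.03 (protocol) | 11.1% | 11.8% |
| 0.05 (assumed) | 15.0% | about 16% |

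**Step 4: interval width.** 1/√1.51 = 0.814 and 1/√1.57 = 0.798, so literal intervals would be about 19–20% too narrow.

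**Step 5: check by simulation.** 20,000 null trials were run with 22 churches, a residual ICC of 0.03, and ordinary ANCOVA without a church term. The rejection rate was 11.0% with 18 per church and 11.7% with 20. A church-level t-test on baseline-adjusted means with 20 degrees of freedom gave 5.1% and 4.9% on the same data.

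**Step 6: how far baseline adjustment helps.** If church means are stable over time, adjusting for each participant's baseline removes part of the clustering. With an ICC of 0.03 and an assumed church-level correlation of 0.8 between baseline and follow-up, the error falls to 8.6% and 9.0%. With a correlation of 0.5 it stays at 11.0% and 12.0%.

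**The case against.** The strongest reply is that the equation is schematic. The protocol calls it basic. The surrounding text describes longitudinal outcomes, covariates and interactions, none of which appear in it, so it cannot be the complete model. The power section for the same aims uses the same ANCOVA-type label and does carry the church effect. A fuller protocol or analysis plan may spell the model out.

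Much of this stands, and it limits what can be claimed. A reader might infer that DIS and LS7 will be tested as if individuals had been randomised. The protocol does not support that: it nowhere says clustering will be ignored, and its power section points the other way. A reader might also infer that the two LS7 records per person will be treated as independent. That is not supported either, because the power section sets out correlation structures across waves.

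The size is open to challenge too. The ICC of 0.03 is introduced for the binary primary outcome and carried over to DIS and LS7, and a doubling of the error rate does not hold at the lower end of the ICC range.

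What does not stand is that nothing needs correcting. This is not a detail left to another document. The article prints an explicit analysis equation that conflicts with its own power model and with its unit of randomisation, and the only clustering sentence in the analysis text belongs to Aim 1.

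**Conclusion.** The point holds as a contradiction between two models for the same outcomes. The analysis equation for Aims 2 and 3 omits the church effect that the power model includes and that the design requires.

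The type I error of 11–12% rests on three conditions: the equation is fitted as printed, the protocol's ICC of 0.03 applies to DIS and LS7, and baseline adjustment does not absorb much of the church variation. Relaxing the last two gives a range from about 7% to 16%. Every scenario examined exceeds 5%.

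The primary outcome is not affected, since its analysis states that church clustering is modelled. The defect concerns the secondary outcomes and should be corrected before they are analysed.

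**What to change.** Replace the equation under Analysis for Aims 2 and 3 with one that matches the power section. For participant i in church c at follow-up t:

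Y_ict = β0 + β1·Y_0ic + β2·arm_c + time_t + (arm × time)_ct + τ_c + e_ict,

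where τ_c is the church random effect and the e_ict of one participant are correlated across 6 and 12 months. For DIS at 6 months the time terms drop out; they are needed again in the planned sensitivity analysis that adds the 3-month wave.

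State small-sample inference for the arm effect suited to 22 churches, for example Kenward-Roger. It should agree with how the size matching of churches is handled. A fixed 20 degrees of freedom would fit an unmatched analysis (22 − 2) but may not suit one that keeps matched sets.

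The cost is a short change of wording and, in Proc Mixed, one statement for church and one for repeated measures. Compared with literal fitting, intervals become about 23–25% wider at an ICC of 0.03 (√1.51 = 1.23, √1.57 = 1.25), and correctly so. No change to the planned sample size follows from this point, because the power calculation already includes g = 1.57.
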